### Recruitment

Screening and recruitment will be performed during the preoperative anaesthesiology consultation. The screening visit takes place between 2 months and no later than the day before the inclusion visit (Table 1). As each centre has more than 200 patients who undergo a high-risk abdominal surgery each year, we expect 40% of the eligible patients to accept to participate in the study. The high recruitment is because of our study being considered as a quality improvement project where at one point the haemodynamic management is changed for a potentially better strategy (i.e. AFM-based goal-directed fluid therapy (GDFT)).

**Table 1 tbl1:** Study timeline summary.

	Selection visit −2 months to day −1	Inclusion Day −15 to day −0	Intervention Day 0	Follow-up visit at day +30	Follow-up visit by phone at day +90
Verification of inclusion and exclusion criteria	X				
Informed consent	X				
Signature of consent	X				
Medical history or comorbidities		X			
Clinical examination		X			
Anaesthesiology consultation		X			
Intraoperative data			X		
Assessment of and morbidity and mortality				X	X
Assessment of mortality					X

### Randomisation

Randomisation will be performed using block randomisation with a sequence generated in Stata software (version 13; StataCorp) by an independent statistician. The randomisation will be stratified to ensure an alternation of low–medium-volume centres and high-volume centres. The randomisation list will be uploaded into the web-based CleanWeb® (Télémédecine, Boulogne-Billancourt, France) electronic case report form (eCRF) software and forwarded to the sponsor's quality assurance team for validation.

The eCRF (CleanWeb®) also provided clinicians with reminders about the current period (standard of care or AFM). Patients and investigators will not be blinded to treatment allocation. Centres will be notified of their randomisation status only 1 month before transitioning from the standard of care to AFM implementation. This time will be required to upgrade their existing haemodynamic monitoring devices with the AFM software (Edwards Lifesciences).

### Blinding and procedures to minimise bias

Because it is not possible to predict which operations will occur during a cluster's time period and all patients within that period receive the same intervention, selection bias is unlikely. Although it is not feasible to keep physicians blinded throughout the study, research personnel responsible for filling up/managing the eCRF will remain blinded to the intervention period, as they will not be informed about its timing.

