## Ethics and dissemination

The study protocol (APHP220817) has been approved by a French ethics committee (Comité de protection des personnes Sud-Est II, Lyon) on 12 May 2023. All non-French participating centres have also full ethical approval. The study was also registered prospectively on ClinicalTrials.gov under the number NCT06011187 on 25 August 2023. Written informed consent will be obtained from all patients included in this study by investigators. The following article adheres to the SPIRIT statement (Supplementary material 1).

Upon completion of this work, a manuscript will be submitted for publication in a high-impact factor journal. We may also carry out *post hoc* analyses on study data. This work will also be presented at international scientific conferences. Sensible requests for data sharing will be considered by the study director only if they guarantee to preserve the confidentiality of the information requested. Authorship of manuscripts submitted for publication will follow the criteria defined by the International Committee of Medical Journal Editors. Authors' appearance will be based on the number of patients recruited at their centre, as predefined by the study director.

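### Giving everyone in a period the same treatment does not make selection bias unlikely, and the primary model has no patient-level covariate to guard against differential recruitment

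*Protocol article*

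**What the plan says.** The section on blinding and minimising bias gives two grounds for its reassurance: nobody can foresee which operations will fall in a centre's period, and "all patients within that period receive the same intervention, selection bias is unlikely".

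Other sections describe how patients enter the trial:

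- **Consent** (Ethics and dissemination): "Written informed consent will be obtained from all patients included in this study by investigators".
- **Uptake** (Recruitment): "we expect 40% of the eligible patients to accept to participate in the study".
- **Timing** (Recruitment): "The screening visit takes place between 2 months and no later than the day before the inclusion visit". Table 1 places the signature of consent at that selection visit. Eligibility is limited to elective surgery.
- **Knowledge of the arm** (Randomisation): "Patients and investigators will not be blinded to treatment allocation". The eCRF "also provided clinicians with reminders about the current period (standard of care or AFM").
- **Notice of the switch** (Randomisation): "Centres will be notified of their randomisation status only 1 month before transitioning from the standard of care to AFM implementation".

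The Statistical analysis section is not silent on selection. It summarises patients and clusters by group with selection bias expressly in mind, and compares important patient characteristics within clusters by period. The primary model has fixed effects for intervention, step, period and their interactions, and random effects for centre and time. A separate multivariable analysis adds covariates chosen from baseline imbalance and clinical relevance. Those named are surgery type, ASA score, comorbidities and compliance with AFM.

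**The concern.** The bias section answers a question about predicting an individual's allocation. The usual threat in a cluster trial with individual consent is different: the mix of patients approached, or agreeing, may change once the arm is known. A common treatment throughout a three-month period does not prevent this. It is what allows the arm to be known before the patient is approached.

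Randomising the switch dates protects the comparison of centres and calendar time. It does not protect the comparison of enrolled patients before and after a centre's own switch. A change in mix at that point coincides with the intervention indicator, so neither period effects nor centre effects remove it. Baseline covariates in the primary model would remove the part carried by measured risk factors, but none is planned there. At stake is whether a difference in the composite outcome can be read as an effect of AFM.

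**Working it through.** **1. The stated grounds against the trial's own procedures.**

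- *Operations cannot be predicted.* Surgery is elective, consent may be signed up to two months ahead, and periods last three months. The phase in which a scheduled operation will fall is therefore usually foreseeable.
- *One treatment per period.* Together with no blinding of patients or investigators, and eCRF reminders of the current period, this makes the arm known rather than concealed.
- *Room for selection.* 1 − 0.40 = 0.60, so about 60% of eligible patients are expected not to enrol.

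**2. How far the one-month notice limits this.** If consent precedes surgery by at most two months and notice is one month, a signature can precede the notice only for operations in the first 2 − 1 = 1 month after a period boundary. If the two months run back from an inclusion visit 15 days before surgery, the limit is about 1.5 months. Even then it covers only patients who sign early. Such patients exist near each boundary at centres still in the control phase, but they are a minority.

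**3. The design figures.** The planned difference is 46.5 − 36 = 10.5 points. Taking 16 centres, eight periods, seven steps (assumed to hold 2, 2, 2, 2, 2, 3 and 3 centres), 1680 patients (1680 / 128 = 13.125 per centre-period) and ICC 0.01, the Hussey–Hughes variance gives a standard error of 0.0355 and power of 84%. This agrees with the stated power above 80%. The dropout allowance also reproduces: 1680 / (1 − 0.16) = 2000.

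**4. Illustrative size of bias.** The documents give no risks by stratum and no shift in mix, so these are assumptions: risks of 60% and 35%, no treatment effect, and an overall control risk of 46.5%. The implied high-risk share is (0.465 − 0.35) / (0.60 − 0.35) = 0.46.

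Bias = shift in high-risk share × (0.60 − 0.35). Two-sided error = Φ(−1.96 + bias/0.0355) + Φ(−1.96 − bias/0.0355).

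| Shift in share | Bias (points, either sign) | Share of 10.5 | Error of a nominal 5% test |
|---|---|---|---|
| 5 points | 1.25 | 12% | about 6% |
| 10 points | 2.50 | 24% | about 11% |
| 15 points | 3.75 | 36% | about 18% |

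The error column is a normal approximation on the risk-difference scale. The planned model reports relative risks.

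**5. What uptake would produce such shifts.** Suppose half of eligible patients are high-risk and uptake is 40% in both strata before the switch. Uptake of 45% in low-risk and 35% in high-risk patients afterwards gives a high-risk share of 0.35 / 0.80 = 0.4375, a shift of 6.25 points. Uptake of 50% and 30% gives 0.30 / 0.80 = 0.375, a shift of 12.5 points. Overall uptake stays at 40% in both cases, so the total alone would not reveal the change. With strata at 31.5% and 61.5%, the biases are 0.0625 × 0.30 = 1.9 points and 0.125 × 0.30 = 3.8 points. Reversing the uptake pattern reverses the sign.

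**6. The planned adjusted analysis.** It overlaps with what is needed, but has three weaknesses as the safeguard. It is not primary. Its covariates depend partly on the imbalance observed. It lists AFM compliance, which is determined after allocation and is not defined for control patients, who do not receive AFM.

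**The case against.** The best defence is that the plan already deals with selection. It compares baseline characteristics by group and by cluster and period, and it has an adjusted analysis built on nearly the covariates one would ask for. An unadjusted primary model supported by an adjusted one is a defensible choice, and the exact covariate list is commonly left to a statistical analysis plan, which is not shown here. This largely stands, so it would be wrong to say that the plan ignores selection. It does not rescue the reasoning in the bias section. Nor does it alter what the article itself fixes: covariates picked partly from imbalance, with a post-allocation variable among them.

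Four stronger readings are tempting and are not supported:

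- *Every recruiter knows the arm at consent.* Some patients may sign before the one-month notice.
- *The appeal of the new strategy works only after the switch.* The Recruitment section describes the whole study as a quality improvement project in which "haemodynamic management is changed for a potentially better strategy". It does not say that patients are told different things, or accept at different rates, by phase.
- *The bias favours AFM.* Nothing in the documents indicates a direction. Higher-risk patients might enrol more readily under AFM, which would bias against it.
- *No screening log is kept.* A condensed article commonly leaves this to the full protocol, so its absence here shows nothing.

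The blinding of eCRF staff is a real measure, but it bears on data capture, not on who is recruited.

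**Conclusion.** The concern holds as a risk, not as demonstrated bias. The assurance that selection bias is unlikely does not follow from the procedures described: individual consent, 40% expected acceptance, and unblinded patients and investigators who usually know the phase. Baseline comparisons and a secondary adjusted analysis are planned, but the primary comparison has no patient-level adjustment and the secondary analysis is not well specified for this purpose.

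Size and direction are unknown. The range of 1.3 to 3.8 points either way rests wholly on assumed stratum risks of 60% and 35% and an assumed shift of 5 to 15 points. It shows that moderate shifts would matter against a 10.5-point target. It is not an estimate of what will happen.

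**What to change.** 1. **Wording.** Qualify or remove the sentence on selection bias. Say that allocation is usually known at consent and that differential recruitment is possible.
2. **Primary model.** Before analysis, prespecify a fixed set of collected baseline prognostic factors in the primary model: type of surgery, ASA score, age and named comorbidities. Leave AFM compliance out and do not select on observed imbalance. Keep the unadjusted model as a sensitivity analysis.
3. **Reporting.** Where existing screening records allow, report eligible and included patients by centre and period, so that changes around each switch can be seen.

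The cost is slight extra analysis work and the need to settle the covariate list before analysis. Adjustment removes only the part of any bias carried by measured factors, which is why the third item matters. Changing the consent process or starting a new prospective log is not proposed. Recruitment began on 1 February 2024 under approved written consent in four countries, and such changes would reach only patients not yet enrolled.

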### Data collection

Data will be recorded by research staff directly in the eCRF. The data will be collected in a centralised eCRF platform (CleanWeb, Télémédecine). An experienced data manager of the University Paris-Saclay Research Service will program this clinical data base and validate the data quality. Data will be collected from all included patients regardless of the allocated intervention or not.

### Statistical analysis

Analyses will be performed using Stata software (version 15, StataCorp). Baseline characteristics (centres and patients) will be presented as the mean and standard deviation or the median and interquartile range for each intervention group for continuous data and as the number of patients and associated percentages for categorical parameters. The results will be expressed using standardised differences and 95% confidence intervals (95% CIs). The characteristics of the patients and clusters will be summarised by intervention group to allow consideration for selection biases and lack of balance. Patients will be described and compared between intervention groups at baseline for eligibility and epidemiological, clinical, and treatment characteristics. Protocol deviations and reasons for withdrawal will be described. Other parameters such as the numbers analysed, the average cluster size, cluster characteristics, and important patient characteristics will be compared in each cluster by period. Analysis will be done according to the intention-to-treat principle.

To compare the incidence of the primary endpoint, a robust random effect Poisson generalised linear mixed model regression with robust variance will be proposed. Intervention groups, steps of randomisation, time periods—treated as categorical variables—and their interactions will be evaluated as fixed effects and centre and time as random effect. Results will be expressed as relative risks and 95% CIs. The estimated intra-cluster correlation and time effect from the fitted model will be reported. Multivariable analysis will use the same statistical model with covariates determined according to unbalanced baseline and to the clinical relevance (type of surgery, ASA score, comorbidities, and AFM compliance). Furthermore, interaction terms in the regression model will be used to test for heterogeneity of effect between subgroups: type of surgery, ASA score, comorbidities, AFM compliance, and anaesthesia duration. Between-group comparisons for other endpoints will be performed using same random effects models taking into account between- and within-centre and time variability (if necessary to obtain a normal distribution, a logarithmic transformation will be considered) or generalised linear. The time-to-event curves will be calculated with the Kaplan–Meier method and compared, when appropriate, using marginal Cox proportional hazards regression model taking into account between-and within-centre and time variabilities (90 days mortality). No missing data are expected for the primary endpoint. For the secondary endpoints, the statistical nature of missing data will be studied, and sensitivity analysis will be proposed to analyse the impact of missing data on results and propose the most appropriate method of imputation. More precisely, missing data mechanisms will be evaluated to determine if data are missing completely at random (MCAR), at random (MAR), or not at random (MNAR). Multiple imputation methods will be considered for handling MAR data, and sensitivity analyses (e.g. complete case analysis, worst-case imputation) will assess the robustness of results.

All analyses will be performed using Stata software (StataCorp). The widths of CIs will not be adjusted for multiplicity and cannot be used in place of hypothesis testing.

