**Figure 1 fig1:**
[figure not shown]
Stepped-wedge study design of the PEFLA trial. Considering the number of participating centres (16 centres) and the duration of this study (24 months), it was proposed to fix eight intervals of 3 months each. The randomisation will involve seven steps, each of them including two to three centres.

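### The by-arm baseline comparison named as the selection-bias check mixes any recruitment shift with centre mix and a calendar gap of about 9 months; a centre- and period-adjusted contrast should take its place

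*Protocol article*

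**What the plan says.** All references are to the protocol article.

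- Statistical analysis gives the by-arm summary an explicit purpose: "The characteristics of the patients and clusters will be summarised by intervention group to allow consideration for selection biases and lack of balance".
- The metric is set just before: "The results will be expressed using standardised differences and 95% confidence intervals". No adjustment for centre or period is stated for this comparison.
- The comparison is repeated at patient level: "Patients will be described and compared between intervention groups at baseline for eligibility and epidemiological, clinical, and treatment characteristics".
- A second display follows: "cluster characteristics, and important patient characteristics will be compared in each cluster by period". It is not linked to selection bias, and no summary measure is named for it.
- The multivariable model then uses "covariates determined according to unbalanced baseline and to the clinical relevance", so observed imbalance has a downstream use.
- The primary outcome model, in the same section, does include centre and categorical time period.

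The sections on recruitment, randomisation and blinding add context. Patients consent individually and about 40% of those eligible are expected to accept. Patients and investigators are not blinded to allocation, and each centre learns of its switch one month ahead. The article nevertheless regards selection bias as unlikely.

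**The concern.** When patients are individually randomised, both arms share the same centres and the same calendar time in expectation, so a by-arm table is a fair place to look for selection. A stepped wedge breaks that link. Early-switching centres supply mostly AFM patients and late-switching centres mostly control patients, and AFM patients come later. A difference between the arms can therefore arise with no selection, and a real change in who is recruited at the switch can be offset by an opposite centre or calendar difference.

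The quantity of interest is the change in patient mix at a centre's switch beyond the common time trend. The by-arm table does not estimate it. The cluster-by-period comparison contains the relevant data, but it is spread over many small cells with no summary contrast at the switch.

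Two things are at stake. One is the reader's judgement about selection bias in an open-label trial with individual consent. The other is the covariate set of the multivariable model, which could be driven by imbalance that only reflects the rollout.

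**Working it through.** **Inputs from the article.** There are 16 centres; "it was proposed to fix eight intervals of 3 months each"; and "The randomisation will involve seven steps, each of them including two to three centres". Sixteen centres over seven steps means five steps of two and two steps of three. The sample size section gives about 15 patients per centre and period, and 1680 evaluable patients, which is 1680/128 = 13.1 per cell.

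**Assumed inputs (not in the article).** A binary baseline trait with 40% prevalence; trait ICC 0, 0.01, 0.05 or 0.1; drift in prevalence of 0 or 10 points over the 24 months; coefficient of variation of centre size 0 or 0.5; no recruitment bias. The article's ICC range of 0.005–0.05 is not given for baseline traits.

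**Step 1: calendar gap.** Averaging the period number over control and AFM cells:

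| Steps with three centres | Control | AFM | Gap |
|---|---|---|---|
| 1 and 7 | 3.08 | 5.92 | 2.84 periods = 8.5 months |
| 4 and 5 | 2.97 | 6.08 | 3.11 periods = 9.3 months |

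**Step 2: centre mix.** A step-1 centre gives 7 AFM periods and 1 control period; a step-7 centre gives the reverse. With three centres at steps 1 and 7, each arm has 64 cells. A centre with *a* AFM periods has weight difference (2a − 8)/64. The squared numerators sum to 3×36 + 2×16 + 2×4 + 0 + 2×4 + 2×16 + 3×36 = 296, so the multiplier on the between-centre SD is √296/64 = 0.269.

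**Step 3: false-alarm rate of the pooled 95% CI, by hand.** Each arm has 64 × 15 = 960 patients, so the naive SE is √(2 × 0.24/960) = 0.0224.

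- ICC 0.01: between-centre SD √(0.01 × 0.24) = 0.049; true SD of the difference √[(0.269 × 0.049)² + 0.0224²] = 0.026; P(|Z| > 1.96 × 0.0224/0.026) ≈ 9%.
- ICC 0.05: between-centre SD 0.110; true SD 0.037; P ≈ 24%.
- ICC 0 with a 10-point drift: expected difference (10/7) × 2.84 = 4.1 points, or 1.8 naive SEs; P ≈ 44%.

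**Step 4: simulation of the same design** (1500 trials per scenario, three centres at steps 1 and 7, no selection). The entries are the proportion of trials in which the 95% CI excludes zero.

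| Scenario | Pooled by arm | Adjusted for centre and period |
|---|---|---|
| ICC 0, no drift | 4–5% | 4% |
| ICC 0.01, no drift | 8–10% | 4–5% |
| ICC 0.05, no drift | 23–26% | 4% |
| 10-point drift, ICC 0 to 0.1 | 43–51% | 4–5% |

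Over all scenarios, including ICC 0.1 without drift, the adjusted contrast ranged from 3.5% to 5.3%. The hand results agree with the simulation.

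**Step 5: masking.** Suppose a real 10-point recruitment shift meets an opposite 20-point drift. The pooled table then sees about 10 − (20/7) × 2.84 = 1.9 points. It flagged 18–31% of simulated trials, and the adjusted contrast 68–70%. With the same shift and no drift, the pooled table flagged 92–98% and the adjusted contrast 69–70%. The adjusted contrast is thus less sensitive when nothing confounds the comparison.

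**Step 6: precision of the adjusted contrast.** For the layout with three centres at steps 1 and 7, the sum of squares of the AFM indicator after removing centre and period means is 64 − 41.25 − 44.375 + 32 = 10.375. The SE is 1/√(13.125 × 10.375) = 0.086 SD, or roughly 0.085, against √(2/840) = 0.049 for an unclustered pooled difference. A shift detectable with 80% power is (1.96 + 0.84) × 0.085 = 0.24 SD. Power for a shift of 0.1 SD is about 22%.

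**The case against.** The strongest case against has five parts.

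1. *A by-arm baseline table is ordinary reporting, and the article sets no threshold or decision rule for it.* True. But the article names this summary as the place to consider selection bias, so the choice of display is stated and not merely left to an analysis plan.

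2. *The cluster-by-period comparison already covers this.* In part. A reader might infer that the pooled table is the only display planned; it is not. The cluster-by-period data are the right raw material. However, 128 cells of about 13–15 patients give no single contrast at the switch, and the text does not connect them to selection.

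3. *False alarms depend on assumptions.* This stands. With no centre variation and no trend in a trait, the pooled table keeps its nominal 5% rate. A reader might infer that the table will usually mislead; the article gives no ICC or drift for baseline traits, so that cannot be claimed.

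4. *Judging by an absolute standardised difference above 0.1 would be one-sided.* This also stands. The cut-off is not in the article, and at an SE of 0.085 the adjusted contrast would itself exceed 0.1 about 24% of the time with no selection. The fair comparison is by 95% CI, as used here.

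5. *The primary result is unaffected.* A reader might infer that the primary estimate inherits the confounding of the table. The documents do not support that, since the primary model already includes centre and period.

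**Conclusion.** The concern holds in a limited form. The comparison tied to selection bias is confounded by design with centre mix and a calendar gap of 8.5–9.3 months. With no selection, its 95% CI excludes zero for 4–5% of traits in the most favourable case, 8–10% at trait ICC 0.01, 23–26% at 0.05, and 43–51% with a 10-point drift, while an adjusted contrast stays near 5%. These rates rest on the assumed prevalence, ICC and drift listed above. The confounding itself follows from the rollout and needs no assumption beyond similar recruitment in each cell; how far it disturbs a given trait depends on that trait's centre variation and trend.

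The consequence is minor to moderate. It affects how selection bias is judged and which covariates enter the multivariable model, not the primary estimate. The change is worth making because it is cheap and uses an adjustment the article already plans for outcomes.

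**What to change.** - For each key baseline variable (age, ASA class, surgery type, comorbidities), fit a model with that variable as outcome and with AFM, centre and categorical period as terms. Report the AFM coefficient with its 95% CI, and name this as the selection-bias check.
- Keep the by-arm table, and the cluster-by-period comparison beside it, as description only.
- Do not choose multivariable covariates from pooled by-arm imbalance; fix them in advance on clinical grounds.
- State that the adjusted contrast is read by its interval, not against a 0.1 cut-off, and that an interval including zero does not exclude a small recruitment shift.

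The cost is a few model fits on data already collected. The price is precision: an SE of about 0.085 SD, with 80% power only for shifts of about 0.24 SD.

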### Sample size calculation

On the basis of data from previous published studies from our group, the percentage of patients with at least one major postoperative complication using a standard of care practice varies between 45% and 48.7%. As such, we decided to choose 46.5% as the incidence of postoperative complications in the control group. For a classical randomised trial, 466 patients per group (932 patients in total) are needed to show a 20% relative reduction in the primary outcome (from 45% to 36%), using a power of 80% and (two-tailed) alpha risk of 5%. Of note, the main assumption in randomised controlled trials is that the outcome of an individual patient is completely unrelated to that of any other patient (i.e. they are said to be ‘independent’). This assumption is violated in cluster randomised trials as patients within one cluster (centre in our case) are more likely to respond in a similar manner. A measure of this similarity is known as the intraclass correlation coefficient (ICC). Because of this lack of independence, larger sample sizes are required. The ICC values usually described in the literature and reported by the University of Aberdeen on a database dedicated to ICC (https://www.abdn.ac.uk/hsru/what-we-do/tools/index.php) range between 0.005 and 0.05.

The following criteria must consequently be considered when determining sample size for this study: the randomisation sequence (eight periods for each cluster/centre), time periods (3 months), average number of patients per centre (around 15 patients by period), and the coefficient of variation of cluster size, defined as the ratio of the standard deviation (SD) of cluster sizes. To estimate sample size by considering these additional criteria, Stata (StataCorp, College Station, TX, USA) routine stepped-wedge developed by Hemming and Girling has been used. In our trial, 1680 patients (*n*=840 patients by group) are needed to detect a difference between 46.5% and 36% for an ICC value at 0.01, a two-sided type I error at 5%, and a statistical power greater than 80%. To take into account a possible drop-out rate of at least 16% as 30-day follow-up may be difficult in this population, we will include 2000 patients in total. No planned interim analysis will be conducted during the study.

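### The primary model enters time both as categorical fixed effects and as a random effect; read plainly, the random time term is redundant and no centre-by-period variance is named.

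*Protocol article*

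**What the plan says.** All of this is in the Statistical analysis section of the protocol article, except where stated.

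- Model family: "a robust random effect Poisson generalised linear mixed model regression with robust variance will be proposed".
- Terms: intervention group and randomisation step, then "time periods—treated as categorical variables—and their interactions will be evaluated as fixed effects and centre and time as random effect".
- Reporting: "The estimated intra-cluster correlation and time effect from the fitted model will be reported". One correlation is to be reported.
- Other endpoints: analysed with the "same random effects models taking into account between- and within-centre and time variability". Robust variance is not mentioned again at that point.
- Design (Figure 1 legend): 16 centres and eight quarterly periods, two years in all. On the crossover the legend adds: "The randomisation will involve seven steps, each of them including two to three centres".
- Planning (Sample size calculation): a single ICC of 0.01, taken from a cited range of 0.005 to 0.05. No value is given for the decay of correlation between periods.

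**The concern.** Time appears twice in one model. Once each of the eight periods has its own fixed effect, a random intercept for the same eight periods has nothing left to explain. The centre intercept remains. It treats two patients of one centre as equally correlated whether they had surgery in the same quarter or nearly two years apart.

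In a stepped wedge the treatment contrast is partly a within-centre comparison over time. A centre whose event rate drifts on its own adds variance that a centre intercept alone does not capture, and model-based standard errors can then be too small. The usual remedy is a centre-by-period random effect, and the article names none.

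The same sentence also places interactions among intervention, step and period in the fixed part. Treatment status is fully determined by step and period, so this affects whether the treatment effect can be estimated at all.

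If the wording stands, whoever fits the model must choose both the random structure and the interactions, possibly after data are in.

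**Working it through.** **1. The plan's own figures.** The individually randomised size uses n = [1.96·√(2p̄(1−p̄)) + 0.8416·√(p₁q₁ + p₂q₂)]² / (p₁ − p₂)² with p₁ = 0.45, p₂ = 0.36 and p̄ = 0.405. This gives 465.8, so 466 per group, as stated. The stepped-wedge total is 1680 = 14 × 8 × 15. A centre-intercept model with fixed periods at ICC 0.01 and 46.5% against 36% gives 82.5% power. With 16 centres and the same 1680 patients, power is 81.8% to 84.9%, depending on which steps hold three centres. Both agree with the stated power above 80%. Finally, 1680 / (1 − 0.16) = 2000.

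**2. Redundancy of the shared random period term.** The linear predictor contains β_t + u_t, and the data inform only the sum. In generalised least squares terms, the covariance becomes V + τ²ZZ′, where the columns of Z are the period indicators already in the fixed design. The treatment estimate and its variance therefore cannot depend on τ². Check: 16 centres, 8 periods, 15 patients per centre-period, ICC 0.01, with τ² set to 0, 0.01, 0.1 and 10 times the outcome variance. The treatment-effect variance, in units of outcome variance, was 0.004534 each time with the three-centre steps first and last. With those steps third and fifth it was 0.004924 each time (0.001193 / 0.2423, where 0.2423 = 0.4125 × 0.5875).

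**3. Omitting a centre-by-period variance, model-based errors, correct residual variance.** Inputs: 16 centres; 1680 / (16 × 8) = 13.1 patients analysed per centre-period; ICC 0.01 (planning value) and 0.05 (top of the cited range). CAC is the ratio of between-period to within-period correlation. It is not in the document, so 0.8 and 0.5 are assumptions.

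- True covariance of one centre's period means: ICC·CAC·J + [ICC(1 − CAC) + (1 − ICC)/m]·I.
- Fitted covariance: ρJ + [(1 − ρ)/m]·I with ρ = ICC·CAC.
- R = model-based variance / true variance of the treatment estimate.
- Type I error = 2Φ(−1.96·√R).

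| ICC | CAC | R | Type I error |
|---|---|---|---|
| 0.01 | 0.8 | 0.98 | 5.2% |
| 0.01 | 0.5 | 0.95 | 5.6% |
| 0.05 | 0.8 | 0.90 | 6.3% |
| 0.05 | 0.5 | 0.79 | 8.2–8.3% |

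Three placements of the three-centre steps gave the same picture. Setting ρ to the full ICC instead gives at most 5.0% at ICC 0.01 and leaves the ICC 0.05 rows almost unchanged (6.2–6.3% and 8.1–8.3%). With 15 per centre-period, the ICC 0.05 values rise to about 6.6% and 8.8%.

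**4. The same omission under Poisson without robust variance.** Poisson uses p where a binary outcome has p(1 − p), which overstates the residual variance. At a 41% event rate, type I error falls to about 1.5–3% over the four rows. At a 20% rate and ICC 0.05 it is 3.7% (CAC 0.8) and about 5% (CAC 0.5). Inflation returns only for rarer events at ICC 0.05, for example about 7% at a 5% event rate with CAC 0.5.

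**5. Fixed step-by-period interactions.** Seven steps by eight periods make 56 cells. The design matrix of these cells has rank 56, and still 56 after the treatment column is added. Treatment is a linear combination of the cells, so its effect cannot be estimated.

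**The case against.** The strongest reply is that the wording is ambiguous rather than wrong. The sentence does not say whether random time is crossed with centre or nested in it. The later phrase about variability between and within centres and over time fits a nested term. On that reading the centre-by-period variance is intended, and the exact covariance structure may be settled in an analysis plan that is not shown. This stands: a reader might infer that the component is certainly left out, and the document does not support that. It is not named, and the two phrases need to be made to agree.

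A reader might also infer that the random part is empty. It is not, because the centre intercept remains.

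The named robust variance is a further defence. Clustered on centre, it guards the primary standard error against a wrong within-centre correlation. This largely stands too, with two limits: the article does not state the clustering level, and 16 clusters is few for such an estimator. The word for 'same' models may carry robust variance over to the other endpoints, but the text does not say so.

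The interactions are to be evaluated, which could mean tested rather than retained. That softens the point but does not remove it, since a model containing the step-by-period interaction has no estimable treatment effect against which to evaluate anything.

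**Conclusion.** The point holds as a specification fault of modest consequence. On the plain reading, the random time term does nothing beside the fixed period effects, and no centre-by-period term is written.

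The documents do not support a claim that the primary result would be invalid or its type I error materially inflated. The redundant term leaves the treatment estimate and its variance unchanged, and robust variance covers most of the remaining risk.

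The gain is for endpoints analysed with model-based errors, especially continuous ones such as the Comprehensive Complication Index or length of stay. There the excess is slight at the planning ICC (5.2–5.6%) and noticeable only at the top of the cited range (6.3–8.3%). These figures rest on assumed CAC values of 0.8 and 0.5, equal cluster sizes, a normal test and a correct residual variance. It would be tempting to apply them to every secondary endpoint. For common binary outcomes under Poisson without robust variance, the error goes the other way.

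The interaction wording is separate and sharper: taken literally, it removes the treatment effect from the primary model.

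**What to change.** Before the analysis plan is locked:

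1. Keep categorical period as a fixed effect only.
2. Replace the random terms by centre and centre-by-period (nested in centre), for the primary endpoint and every other endpoint using these mixed models. If the centre-by-period variance is estimated at zero, fall back to the centre intercept.
3. State that the robust variance is clustered on centre and also applies to the other endpoints.
4. Remove fixed step-by-period interactions from the primary model. Changing the random part alone would not make the model estimable as written.

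The cost is a few lines of text and one extra variance component. Intervals will be slightly wider if centre levels drift, and a boundary estimate will occur now and then, which the fallback handles. No design change or additional data are needed.
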